## Abstract

**Background:**

Masculinity norms play a crucial role in men’s help-seeking behaviors, service-use, and coping strategies for depression. While previous studies provided evidence for the association between gender role orientations, work related attitudes, stigmatization of men with depression and depressive symptoms, it remains unclear to what extent gender role orientations change over time and whether psychiatric and psychotherapeutic treatment have an impact on these transformations. Additionally, the role of partners in supporting depressed men and the impact of dyadic coping on these processes have not been explored. The aim of this study is to investigate how masculinity orientations and work-related attitudes change over time in men treated for depression, and to examine the role of their partners and dyadic coping in these transformation processes.

**Methods:**

TRANSMODE is a prospective longitudinal mixed-methods study investigating the transformation of masculinity orientations and work-related attitudes in men treated for depression between the ages of 18 and 65 from different settings in Germany. The study will recruit 350 men from various settings for quantitative analysis. By applying a latent transition analysis, the primary outcome are changes in masculine orientations and work-related attitudes over time, measured at four times (t0, t1, t2, t3) with intervals of 6 months. Qualitative interview with a subsample of depressed men selected using latent profile analysis, will be conducted between t0 and t1 (a1) with a follow-up of 12 months (a2). In addition, qualitative interviews with the partners of depressed men will be conducted between t2 and t3 (p1). Qualitative data will be analysed using qualitative structured content analysis.

**Discussion:**

A comprehensive understanding of the transformation processes of masculinity orientations over time including the impact of psychiatric/psychotherapeutic treatment and the role of partners can lead to the development of gender-sensitive depression treatment tailored to the unique needs of men with depression. Thus, the study can promote more effective and successful treatment outcomes and further contribute to reducing the stigma surrounding mental health issues among men and encourage them for mental health service use.

**Trial registration:**

This study is registered in the German Clinical Trail Register (DRKS) and the WHO International Clinical Trials Registry Platform (ICTRP) under registration number DRKS00031065 (Date of registration 06 February 2023).

## Background

Masculinity norms have been identified as playing a crucial role in men’s coping with depressive symptoms and their willingness to seek professional help [1–5]. In the Gotland study, conducted between 1981 and 1990, Rutz et al. [6, 7] found that traditional masculinity norms explained the paradox that men had a lower frequency of depression [8] but a higher rate of suicides than women [7, 9]. Based on this, several authors developed the concept of male depression, suggesting that in men, depression occurs with different symptoms than those applied in psychiatric diagnosis classification systems such as ICD or DSM [6, 10–12]. Unlike depression in women, male depression is characterized by increased irritability, aggressiveness, anger and antisocial behavior [6, 10, 12, 13]. In addition to these differences, men were also found to mask classical symptoms of depression such as fatigue, sadness, and weariness to avoid being considered unmanly by their social environment [3].

Working conditions have been identified as an important factor in the development and course of depression among both men and women [14–21]. However, research suggests that the impact of work related problems on symptoms of depression may differ between men and women [21]. A study conducted in Canada by Wang et al. [21] showed that job insecurity was positively associated with depression in men but not in women. Similarly, Pyöriä et al. [22] found that precarious employment was associated with an increased risk of future depression in men but not in women in a sample of Finish salary earners. The authors of both studies suggested that men’s “masculine” self-identity might be more strongly linked to paid work and the role as breadwinner, while women’s self-identity might be more rooted in their social skills and their role as members of social networks [21, 22]. This interpretation was supported by results from the WHO mental health surveys, which revealed that the gender difference in depression decreased with decreasing levels of traditional masculinity orientations [8]. However, this interpretation was not supported by the results of a recent meta analyses, which suggested that the gender differences in major depression across countries increase with gender equity [23]. With regard to the male suicide rate, the gender role equity interpretation would be supported by a cross-country analysis of Reeves & Struckler [24], indicating that an increase in gender norm equity was associated with a decrease in the association between unemployment and the suicide rate in men but not in women.

While there is strong evidence that the adherence to traditional male gender norms serves as a barrier to seeking informal and formal help or support for mental health problems, limited knowledge exists about the impact of masculinity norms on post-diagnostic processes and pathways, including depression treatment and/or psychotherapy use. Findings on high drop-out rates among men suggest that men’s needs may not be adequately addressed within therapeutic settings. There is some evidence that men have ambivalent or even critical attitudes towards psychotherapy [25] or antidepressants [26]. An Australian survey revealed that men dropped out due to a lack of therapist-client connection and dissatisfaction with the therapy processes, with some men reporting feelings of emasculation in attending therapy [27]. Eggenberger and colleagues found that reduced psychotherapy use in men with experienced psychological distress was associated with higher self-identified masculinity [28]. However, endorsement of masculinity norms exerts a different impact on men’s mental health treatment utilization: while greater endorsement of the status norm is associated with increased utilization, endorsement of the anti-femininity norm and the toughness norm is associated with decreased service utilization [29]. From male service users’ perspectives, perceptions of autonomy and control in therapeutic interactions are crucial factors for treatment engagement or disengagement [30].

The growing evidence for the detrimental effects of men’s endorsement to traditional masculinity norms is mirrored in mental health professionals’ reflections on the impact of masculinity norms on mental health care. In a German qualitative study, mental health professionals described depressed male patients’ treatment expectations as different from females’ and characterized by preferences for biological explanatory models and “mechanical” approaches. Accordingly, mental health professionals reported addressing the negative effects of normative expectations regarding male gender on men’s mental health during depression treatment [31]. Based on experiences with men’s reluctance to engage in usual therapeutic environments favoring emotional rather than “problem-solving” coping approaches, Westwood & Black describe a specific approach to successfully engaging men in the counselling process by using appropriate language or pro-active approaches [32]. However, despite the efforts to adjust concepts of depression treatment to the particular needs of men, the impact of psychiatric and psychotherapeutic treatment on changing masculinity orientations or work role orientations of men with depression has not been investigated so far.

Beyond the potential impact of professional treatment, traditional gender roles can be changed or modified during the process of couples’ coping with illness. Couples in which a male partner is depressed have been found to co-construct alternative masculinities by recalibrating gender relations [33]. Due to their partners’ failure to correspond to traditional male roles, female partners make adaptations and take on responsibilities in order to “protect their partners and the façade of gender normalcy” [34]. Although earlier research has focused on women’s role as caregivers for diseased male partners [35, 36] there is only limited research on the involvement of partners in coping with men’s depression and the impact of dyadic coping on men’s masculinity orientations and work role orientations.

Several of the studies mentioned above suggest that a masculine self-identity in combination with a traditional job role orientation, may increase men’s vulnerability against adverse job or economic conditions. However, this hypothesis has not been investigated any further so far. Only recently, Kilian et al. [1], in a mixed-method study, identified traditional masculinity norms in combination with a traditional job role orientation as a cognitive pattern associated with an increased level of psychopathological symptoms and also with an increased level of stigmatizing and self-stigmatizing attitudes regarding depressive disorders in a sample of men treated for depression. In the qualitative part of the study, the authors found indications that some of the respondents started to identify their masculinity and work role orientations as a cause of depression and made efforts to change these dysfunctional attitudes [37, 38]. Due to the cross-sectional character of the study, the authors were not able to make conclusions about the causal direction of the associations between masculinity orientations and depressive symptoms and about the role of psychiatric and psychotherapeutic treatment in this association.

In order to better tailor existing depression treatment services for male patients, we need to better understand men’s experiences, attitudes and needs regarding depression therapy. Therefore, the authors designed a longitudinal mixed method study to observe men with depression over a period of 24 months with the purpose of understanding the interrelation between treatment and masculinity orientations.

## Methods/Design

### Study aim

The aim of the TRANSMODE study is to investigate the transformation of masculinity orientations and work-related attitudes in a sample of men treated for depression and their partners. The main objectives are:

To assess different latent classes of masculinity orientations and work-related attitudes of men treated for depression and the changes of the latent classes over time (transformation).To investigate the interplay between the transformation of masculinity orientations and work-related attitudes and depressive symptoms, stigmatizing attitudes, and the use of psychiatric or psychotherapeutic treatment.To investigate the subjective perspectives of men treated for depression on the transformation process and the subjective perceptions of the impact of the treatment on the masculinity orientations and work-related attitudes and vice versa.To explore the subjective perspectives of depressed men’s parters on their partner’s depression and on the co-construction of masculinity orientations and work-related attitudes.

### Study design

This protocol describes a prospective mixed-methods observational study consisting of three parts (subprojects). The mixed-methods-design is realized through the combination of quantitative surveys and qualitative guided interviews and based on the Explanatory Sequential Design [38, 39]. In addition, due to the longitudinal design, quantitative and qualitative data are collected in parallel [40].

As the first part, a quantitative longitudinal observational study including 350 men treated for depression will be conducted with four measurement points over 24 months (subproject 1).As the second part, a qualitative longitudinal study will be conducted including a subsample of approximately 60 participants with two assessement points over 12 months (subproject 2).As the third part, a cross-sectional qualitative study will be conducted, involving appr. 15 partners of the male participants who have been selected for the qualitative longitudinal study (subproject 3).

### Study setting

Study participants will be recruited at the following study sites providing in- and outpatient mental health treatment and care in Germany:

Department of Psychiatry and Psychotherapy II, Ulm University, Bezirkskrankenhaus Guenzburg.Psychosomatic Medicine and Psychotherapy, University Hospital Ulm.Department of Psychiatry, Psychotherapy and Psychosomatics at the University of Augsburg, Bezirkskrankenhaus Augsburg.District Hospital Kempten, Bezirkskrankenhaus Kempten.District Hospital Memmingen, Bezirkskrankenhaus Memmingen.District Hospital Donauwörth, Bezirkskrankenhaus Donauwörth.Kbo-Isar-Amper Hospital, München, Haar, Fürstenfeldbruck.Clinic for Psychiatry, Psychotherapy and Psychosomatics, Heidenheim Clinic.Clinic of Psychiatry, Psychotherapy and Psychosomatic, Imland Klinik Rendsburg.

Furthermore, participants will be recruited via social media (Facebook and Instagram) using paid advertisements, with each advertisement shown to approximately 10.000 men. In addition, recruitment will take place within self-help groups for people with depression, particularly in the south of Germany, but also nationwide.

### Participants and eligibility criteria

Men between the ages 18 and 65 who have been diagnosed with depression and have received treatment for depression in the last 12 months, or are about to receive their first treatment, will be included in the study. Men with a primary diagnosis of an addiction disorder will be excluded. Eligibility criteria will be checked by study workers prior to study inclusion using a screening tool. For inpatients and day hospital patients, the screening will be conducted by the treating physician or psychotherapist.

### Participant timeline

The recruitment period started in May 2022 and continues until June 2023, and the participation period for each participant will be 24 months. Surveys for the quantitative subproject will be conducted at T0 (baseline) and with intervals of 6 months (t0; t1 = t0 + 6months, t2 = t1 + 6months, t3 = t2 + 6months). The qualitative interviews with the participants will be conducted between t0 and t1 (a1) with a follow-up after 12 months (a2). The qualitative interviews with the partners will be conducted between t2 and t3 (p1). The quantitative measurement, resp. qualitative assessement time points of the 3 subprojects are shown in Fig. 1. At the time of the submission of this protocol, n = 324 have been included in the study.

**Fig. 1 Fig1:**
[figure not shown]
Participant timeline

### Outcomes

#### Subproject 1 (quantitative longitudinal observational study)

##### Primary outcome

Primary outcome of subproject 1 is the transition of participants between latent class membership related to masculinity orientations (using MRNS) and work-related attitudes (using the AVEM) between the follow-ups. Data will be collected at t0, t1, t2, t3 at intervals of 6 months.

##### Secondary outcomes

The secondary oucomes include the change in stigmatizing attitudes towards mental illness (using the DSS), the change in depressive symtoms (using the PHQ SADS), characteristics of the treatment process (using the CSSRI) and sociodemographic characteristics in regard with transition between latent classes of masculinity orientations (using the MRNS) and work-related attitudes (using the AVEM), measured at t0, t1, t2, and t3.

#### Subproject 2 (qualitative longitudinal study)

The qualitative study investigates the subjective perceptions of the transformation processes described above at two assessement time points (a1 and a2). Particular attention will be drawn to factors that might affect the changes and the role attributed to depression treatment, such as in the context of psychotherapy and psychiatric or other medical treatment. Furthermore, we will explore (a) how knowledge about depression and therapy is integrated into experiential and everyday knowledge, (b) how this integration enables a transformation towards health-promoting masculinity orientations and positive attitudes towards occupational health and (c) how this affects illness and recovery processes including self-interpretation, world-interpretation, and daily life. In addition, we aim at identifying treatment elements that are perceived as conducive or obstructive for recovery, and the ways in which male gender norms can impact individuals experiencing depression and its treatment.

#### Subproject 3 (cross-sectional qualitative study)

The qualitative study explores the subjective perspectives of the partners of men treated for depression through problem-centered interviews between t2 and t3 (p1) with (female and male) partners of the participants of subprojects 1 and 2. Particular attention will be paid to the partners’ views on changes in their partner’s masculinity orientations and work-related attitudes occurred during the therapy or recovery processes, and on the negotiations of gender roles within the relationship (co-construction of masculinity, or co-coping) within partnerships.

### Recruitment and sample size calculation

#### Subproject 1 (quantitative longitudinal observational study)

A necessary sample size of n = 250 for the quantitative study has be calculated on the basis of simulation studies with regard to the reliability of latent class assignment and latent transition probabilities with a minimal power of 0.80 [39]. Taking into account a total dropout rate of 30%, a sample size of 350 participants has been targeted for inclusion. The recruitment will be conducted from May 2022 to June 2023 in clinical settings, via patient organisations and via social media. For each inpatient setting, clinical staff members have been appointed as contact persons by the chief doctors. Clinical contact persons have been informed about the study details and the eligibility criteria. In addition, information flyers have been laid out at the common hospital areas. Clinical staff members contacted potentially eligible patients and asked them for their consent to pass contact information to research workers. Patient organisations have been contacted, informed about the study, and provided with study flyers for distribution to members by e-mail. Self-help groups that specialise in men’ groups have also been contacted. Participants have been called on to participate at regular intervals via various media, including payed advertisements in social media (Facebook, Instagram), local newspapers, radio and online pages of the BKH clinics and University Ulm.

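### Minor: with 30% dropout, 350 men leave 245, five fewer than the 250 the protocol calls necessary; 350 retains 250 only if dropout is at most 28.6%

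*Protocol article*

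**What the plan says.** The protocol article, under Recruitment and sample size calculation, Subproject 1, gives the reasoning in two consecutive sentences. The first sets the base: "A necessary sample size of n = 250 for the quantitative study has be calculated on the basis of simulation studies". The simulations concern the reliability of "latent class assignment and latent transition probabilities with a minimal power of 0.80". The second moves from the base to the enrolment target: "Taking into account a total dropout rate of 30%, a sample size of 350 participants has been targeted for inclusion".

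The target appears again without qualification. Study design describes "a quantitative longitudinal observational study including 350 men treated for depression", and the Methods part of the abstract gives the same number. No section states how many men are expected to remain after dropout, and no section reconciles 350 with 250 and 30%.

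**The concern.** The base figure is worded as a floor: 250 is called necessary and the power attached to it is a minimum. A reader who meets a floor, a dropout rate and a target in sequence will assume that the target less the dropout returns the floor. Here it does not.

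Two features of the article strengthen that expectation. Study design marks the sizes of the two qualitative samples as approximate but gives 350 plainly. The attrition sum for subproject 2 balances exactly: 60 men with a maximum dropout of 50% leave 30.

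At stake is the accuracy of the only power statement in the article. It concerns transitions between latent classes, which are the primary outcome of subproject 1.

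**Working it through.** **Inputs**, all from the Subproject 1 paragraph of the sample size section:

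- Required number: N = 250
- Total dropout: d = 0.30
- Enrolment target: 350

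**Step 1: reproduce the target.** The standard inflation is N/(1 − d).

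- 250/(1 − 0.30) = 250/0.70 = 357.1, rounded up to 358.
- Check: 357 × 0.70 = 249.9, just short; 358 × 0.70 = 250.6, sufficient.
- The common mistake, N × (1 + d), would give 250 × 1.30 = 325, which is far from 350.

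The printed 350 is therefore close to the correct formula and not to the usual wrong one. The natural reading is that 357.1 was rounded down to a convenient figure. The difference is 358 − 350 = 8 men, or 8/358 = 2.2% of the required enrolment.

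**Step 2: work forward from the target.**

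- Men remaining at 30% dropout: 350 × 0.70 = 245.
- Shortfall against the requirement: 250 − 245 = 5 men, or 5/250 = 2.0%.

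**Step 3: find the dropout that 350 can absorb.**

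- 1 − 250/350 = 100/350 = 0.2857, or 28.6%. The target tolerates the loss of 100 men; 30% of 350 is 105.

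**Step 4: vary the dropout.**

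| Dropout | Men left from 350 | Enrolment needed for 250 |
|---|---|---|
| 28.5% | 250.25 | 350 |
| 29% | 248.5 | 353 |
| 29.5% | 246.75 | 355 |
| 30% | 245 | 358 |

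**Step 5: power.** The base of 250 cannot be recomputed. The article gives no effect size, significance level, class separation or assumed transition probabilities for the simulations. Power at 245 men therefore cannot be calculated and compared with power at 250.

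**The case against.** The best defence is that this is rounding and nothing more. The right formula was used. Both 250 and 30% are round planning figures, and 28.6% is 30% to the nearest ten. A difference of 1.4 percentage points is well within the uncertainty of any dropout forecast over four survey waves. The article never says that exactly 250 men will remain, so no explicit statement is contradicted. The study is observational and descriptive in its aims, and no test turns on 245 against 250.

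Most of this stands, and it limits the point in three ways.

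- **Method.** A reader might infer that the target does not follow from its inputs at all. It does, by the correct formula, to within about 2%.
- **Power.** A reader might infer that power falls below 0.80, or that the power claim is missed. The article supports neither. Without the simulation inputs the power at 245 is unknown, and a 2% change in sample size would usually move it only slightly.
- **Who counts.** A reader might take the 250, or the 245, as men with complete follow-up at all four waves. The sample size section does not define the 250 that way, and the statistical methods section does not restrict the latent transition analysis to complete cases.

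What the defence does not remove is the direction of the rounding. When a number is presented as necessary, rounding the enrolment down goes below it, whereas rounding up to 358 or 360 would have kept it. That the inputs are round explains the gap but does not make the three printed figures agree.

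**Conclusion.** The point holds as a minor correction. Taking the 250 and the 30% at face value, the target of 350 leaves 245 men, 5 (2%) below the stated requirement. Equivalently, enrolment is 8 men short of 358, or the tolerable dropout is 28.6% and not 30%.

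This assumes only that dropout is applied once, as a total, to the men included, which is how the article words it. No conclusion about the achieved power follows, and the design, the outcome and the analysis are unaffected.

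**What to change.** Amend one sentence in the Subproject 1 sample size paragraph. Keep the minimum power of 0.80 attached to 250 men, and then use one of two wordings:

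- 350 men are to be included; at 30% total dropout about 245 would remain, slightly below the 250 planned; or
- 350 men are to be included, which retains 250 if total dropout does not exceed 28.6%.

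Neither wording should add a revised power figure or define the remaining men as having complete follow-up, since the article provides no basis for either.

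The cost is one sentence and a slightly less favourable statement. No new enrolment is needed, and the figure of 350 in the abstract and under Study design can stay.
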